We present the protocol for a superiority, prospective, monocentric, randomized, phase II controlled trial with a 2:1 parallel group design. The primary objective of this trial is to evaluate the impact of osteopathic visceral mobilizations on postoperative quality of life in women undergoing surgery for endometriosis. Intervention includes postoperative consultations with an experienced osteopath and training in abdominal self-mobilization, with outcomes assessed at 12 months post-surgery. Secondary objectives include comparing patient quality of life at 6 and 12 months post-surgery, post-operative pelvic pain, scar appearance, abdominal flexibility, range of medical and non-medical care, use of analgesics and hormonal treatments, pregnancy achievement documented at 12 months, physical activity and sedentary lifestyle and patient compliance throughout the study.

This protocol provides a robust framework for investigating the effectiveness of osteopathic interventions in improving postoperative outcomes and quality of life in this patient population.

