### Study design and participant timeline

The flow chart of the study is presented in **Fig 1**. This is a superiority monocentric 2:1 randomized parallel group trial comparing reported quality of life, using the 30-item Endometriosis Health Profile (EHP-30) questionnaire, in 2 groups of patients operated for endometriosis. In the experimental group, patients receive pre and post-operative osteopathic consultations. The pre-operative consultation includes learning abdominal self-mobilizations and abdominal diaphragmatic respiration with the osteopath. The 5 post-operative consultations, occurring at 3–5 day intervals, involve visceral mobilizations performed by the osteopath (D6, D10, D14, D18 and W6). In the second group (control group), patients receive no osteopathic mobilizations (**Fig 2**).

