#### Osteopathic interventions.

Patients in the experimental group will receive training in abdominal self-mobilizations at an initial pre-operative consultation, to ensure they can perform these techniques independently and take an active role in their treatment. While some maneuvers remain managed by the osteopath, patients are required to perform frequent sessions of self-mobilization of the abdomen, combined with Abdominal Diaphragmatic (AD) breathing. AD breathing, the self-mobilization procedure and osteopathic intervention are detailed in appendix 1 and 2.

Patient participation allows:

Optimization of treatment provided by the osteopath, who cannot be seen every dayPain management using the simple tools available to patientsAssociation of this part of the body with sensations other than painPatients to take an active role in their treatment.

Patients in the intervention group receive six sessions with the osteopath.

**Session 1** Pre-surgical session focusing on the teaching of self-mobilization **(****Appendix 1**)

AD breathing in 6 stepsAbdominal self-mobilization of:Three lower abdominal regions: right iliac fossa, hypogastrium and left iliac fossaAbdominal scarsSequence of maneuvers and repetitions:Ten AD breathsAbdominal self-mobilizations (of the 3 regions + scars)10 AD breaths

The procedure is to be repeated 3 times a day during the first month.

In the first postoperative week if self-mobilizations are difficult to perform (e.g., high pain levels or apprehension), the patient will perform AD breathing more frequently, namely 6 cycles of 10 AD breaths per day.

**Sessions 2–6** (D6, D10, D14, D18 and W6): Visceral mobilizations by the osteopath are performed during the month following surgery, with sessions at 3–5-day intervals (Appendix 2, **Fig 1** and **Fig 2**).

During these consultations, the osteopath ensures self-mobilizations are being correctly carried out, readjusts if necessary and answers any patients questions. The osteopath also checks that patient follow-up notebooks are completed.

These sessions also involve:

a/Achieving a balanced diaphragmatic rangeb/General abdominal mobilizations: hypogastric zones and right and left iliac fossaec/Abdominal scar manipulationd/Maneuver stages:Ten AD breathsWork on achieving balance in diaphragmatic rangeGeneral abdominal mobilizationsTen AD breaths

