### Outcomes

The primary outcome is the percentage variation in baseline EHP30 questionnaire scores between the pre-operative visit and at 1 year after surgery.

To measure QoL, the authors chose the EHP-30 questionnaire, one of the most frequently used scales for quantification of perceived health, specific to endometriosis [11].

The EHP-30 contains 30 items ranging from 0 (best health status) to 100 (worst health status). The core questionnaire items are grouped into 5 main scales: pain (11 items), control and powerlessness (6 items), emotional well-being (6 items), social support (4 items) and self-image (3 items). A modular questionnaire, that may not apply to all women with endometriosis, comprises 23 items grouped into six scales: ‘Work’ (5 items), ‘Relationship with children’ (2 items), ‘Sexual intercourse’ (5 items), ‘Medical profession’ (4 items), ‘Treatment’ (3 items), and ‘Infertility’ (4 items) [7].

Secondary outcomes are listed below:

1/- a/The following validated questionnaire scores: EHP-30, GIQLI (digestive function), FSFI (sexual function), ICIQ-FLUTS (urinary tract symptoms) and PCS (pain catastrophizing) evaluated at the pre-operative visit, and at 6 and 12 months.- b/VAS of pelvic pain reported at the pre-operative visit, then post-operatively at H6, D1, 1 month, 6 and 12 months and expressed as a percentage variation compared with pre-operative visit results.-c/Post-operative examination of scar appearance by the surgeon at 6 and 12 months using the SCAR (Scar Cosmesis Assessment and Rating) scale.2/- a/VAS of abdominal flexibility in the following areas: hypogastrium, and right and left iliac fossa, at one year assessed by an independent osteopath, scores ranging from 0 to 10 (0 corresponding to normal flexibility and 10 to total rigidity).- b/Consultations in addition to conventional care (medical and non-medical)- c)Use of analgesics and hormonal treatments reported by patients during the first postoperative year-d)Pregnancy achievement during the first postoperative year3/The International Physical Activity Questionnaire (IPAQ) assessed before surgery, at 6 and 12 months after surgery.4/Short-term compliance in terms of number of days and frequency of mobilizations, assessed on a weekly basis for up to 6 weeks,. Long-term compliance is assessed monthly post-cycle in terms of whether and how often mobilizations were performed, and if used in cases of pain.

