### Statistical methods

Statistical analyses will be carried out using R software (R Core Team (2022). R: A language and environment for statistical computing. R Foundation for Statistical Computing, Vienna, Austria. URL https://www.R-project.org/.).

Descriptions are given in number (N) and percentage (%) for qualitative variables, and in mean and standard deviation (SD) or median and interquartile range for quantitative variables, according to their distributions (Gaussian or not). Missing data will be quantified. Normality will be analyzed using the Shapiro-Wilk test and histograms.

Patients will be described and compared between groups at inclusion according to compliance with eligibility criteria, epidemiological characteristics and clinical features. A description of protocol deviations, patients allocated according to these deviations and reasons for drop-out will also be provided.

Initial comparability of the two groups will be assessed on the main patient characteristics and potential factors associated with the primary endpoint. Any difference between the two groups relating to these characteristics will be determined on the basis of clinical and statistical considerations.

Comparisons between groups will be made systematically 1) without adjustment 2) by adjusting for those factors for which distribution may be unbalanced between groups despite randomization, such as contraception, level of disease severity and post-operative complications. All statistical tests will be performed using a two-sided alpha level of 5%. Certain analyses involving secondary endpoints will be mainly exploratory in nature. As discussed by Feise et al. [47] adjustment of alpha risk will not be proposed systematically, but on a case-by-case basis in the light of clinical and statistical considerations.

The main analysis will be carried out on an intention-to-treat basis. An intention-to-treat population refers to all randomized patients except those for whom consent is not obtained or who withdraw their consent concerning use of their data. A per-protocol analysis will be considered of all randomized patients except for those with one or more major deviations defined as: patients ineligibility, uncompliant patients in the experimental group (less than once a day on average over the first post-operative month), or control group patients who perform visceral mobilizations more than 4 times during the year of their own initiative.

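### The per-protocol definition ignores attendance at the osteopath sessions, and its control-arm rule does not say whose mobilisations count

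*Protocol article*

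**What the plan says.** The Statistical methods section of the protocol article makes intention to treat the main analysis and says that a per-protocol analysis will be considered. The per-protocol set is "all randomized patients except for those with one or more major deviations defined as" three things: ineligibility; "uncompliant patients in the experimental group (less than once a day on average over the first post-operative month"); and "control group patients who perform visceral mobilizations more than 4 times during the year of their own initiative".

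The Introduction states the aim: "The primary objective of this trial is to evaluate the impact of osteopathic visceral mobilizations on postoperative quality of life". On the treatment itself, Study design and participant timeline says that the five post-operative consultations "involve visceral mobilizations performed by the osteopath (D6, D10, D14, D18 and W6"). Osteopathic interventions adds "Patients in the intervention group receive six sessions with the osteopath", one pre-operative and five post-operative. For the patient's own practice, the same section says "The procedure is to be repeated 3 times a day during the first month".

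Under Outcomes, compliance is described as "Short-term compliance in terms of number of days and frequency of mobilizations, assessed on a weekly basis for up to 6 weeks". Attendance at the osteopath sessions is not part of that measure.

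**The concern.** A per-protocol set is normally read as the patients who received the treatment substantially as planned. Here the treatment has two parts: mobilisation by the osteopath in scheduled sessions, and self-mobilisation by the patient. The set tests only the second part. The part named in the primary objective can be wholly absent without making a patient a major deviation.

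The control side has a matching weakness. If controls seek osteopathic treatment outside the trial, the set should identify them, but the wording leaves it open whether such treatment counts. This is a realistic possibility on the protocol's own terms: the Discussion calls osteopathy essential to endometriosis care, and the regression analysis lists previous osteopathic mobilisation as a covariate.

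What is at stake is the meaning of the per-protocol estimate. Experimental patients without sessions and controls treated by a practitioner could both be counted as adherent, and both would tend to shrink the contrast that the analysis is meant to show.

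**Working it through.** The plan gives no figure for the per-protocol set, so the check is to apply the written rule to the written intervention.

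**Inputs**
- Post-operative osteopath sessions: 5, at D6, D10, D14, D18 and W6 (Study design and participant timeline).
- Self-mobilisation in the first month: 3 times a day (Osteopathic interventions).
- Experimental-arm cut: below once a day on average over the first post-operative month (Statistical methods).
- Control-arm cut: more than 4 times in the year (Statistical methods).
- Difference used for planning: 20 points (Sample size).

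**Step 1. What the daily rate measures.** Four of the five sessions (D6 to D18) fall within a 30-day month, and 4 / 30 = 0.13 per day. If the cut counted osteopath sessions, every experimental patient would fail it. It must therefore refer to self-mobilisation. If it counted both kinds together, a patient with no sessions would still pass with 30 self-mobilisations in 30 days.

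**Step 2. The experimental arm under the rule.**

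| Eligible patient | Self-mobilisations in 30 days | Osteopath sessions | Status |
|---|---|---|---|
| A | 90 (3 × 30) | 5 of 5 | retained |
| B | 90 | 0 of 5 | retained |
| C | 30 (1 × 30) | 0 of 5 | retained |
| D | 29 | 5 of 5 | excluded |

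The rule keeps B and C, who had no mobilisation by the osteopath after surgery, and removes D, who had all of it.

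**Step 3. The control arm under two readings.**

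| Reading of the control rule | 4 self-mobilisations | 5 self-mobilisations | 5 practitioner sessions |
|---|---|---|---|
| Self-mobilisation only | retained | excluded | retained (not counted) |
| Practitioner treatment also counts | retained | excluded | excluded |

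The text does not choose between the readings. Under the first, a control could have any number of osteopath sessions and remain per-protocol.

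**Step 4. Possible size (illustration only).** The documents give no attendance rate. Let f be the share of retained experimental patients without sessions and l the share of the benefit they lose. The difference is then 20 × (1 − f × l).
- f = 0.10, l = 0.5: 20 × 0.95 = 19 points.
- f = 0.20, l = 1.0: 20 × 0.80 = 16 points.
- f = 0.30, l = 1.0: 20 × 0.70 = 14 points.

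**Step 5. Are the data available?** Study design and participant timeline says that data are collected at the five post-operative osteopathic interventions, and that the booklet records medical and non-medical treatment in both groups. Attendance is therefore derivable from planned data. Practitioner treatment of controls is too, provided the booklet identifies the type of care.

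**The case against.** The strongest reply is that this touches only an optional secondary analysis. The main analysis is by intention to treat, and protocol deviations are to be described in any case. That stands: the primary result is not at risk, and the supportive status of the per-protocol analysis is already there in substance.

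A second reply is that self-mobilisation is itself part of the tested treatment, as the Abstract's objective says. That also stands in part. A patient with no sessions who practises daily is not untreated, and she is retained only if she is eligible and meets the daily cut. But she has not had the treatment as described, and the rule cannot tell her from someone who has.

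A third reply is that an article condenses its protocol. It does not help here, because the deviations are given as a definition and not as examples.

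Four stronger readings are tempting, and the documents do not support them.
- **Controls may receive 80% of the post-operative sessions (4 / 5).** This needs the rule to mean practitioner sessions. Read as self-mobilisation, four in a year against 90 in the first month is about 4% (4 / 90), which is trivial. The defensible point is the ambiguity.
- **The cut is wrong because it is one third of the stated frequency (1 / 3).** A per-protocol minimum below the full schedule is ordinary, and nothing in the documents makes this one an error.
- **The rule breaks the randomised comparison because it selects in one arm.** That is true of any per-protocol set built on adherence after randomisation, including one with an attendance rule. It is a reason to keep the result supportive, not a defect peculiar to this rule.
- **A complier-average estimate, with session attendance as receipt of treatment, would repair it.** Allocation also delivers the pre-operative training and the self-mobilisation, so it can affect outcome by routes other than attended sessions. The exclusion restriction would fail.

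**Conclusion.** The point holds in a limited form. As written, an eligible experimental patient averaging at least one self-mobilisation a day is per-protocol with 0 of 5 post-operative osteopath sessions, and the control rule leaves it undecided whether treatment by a practitioner counts. The first follows from the wording together with the session schedule. The second is an ambiguity, not proof that treated controls are kept.

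The consequence is confined to the interpretation of a supportive analysis. Its size cannot be fixed from the documents. The range of 19 to 14 points against 20 rests on assumed shares of 10% to 30% without sessions and an assumed loss of half to all of the benefit. If attendance is near complete and controls do not seek osteopathic care, the effect is negligible.

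**What to change.** Before analysis, make two changes to the list of major deviations.

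1. Add insufficient attendance at the five post-operative osteopath sessions as a major deviation in the experimental arm. The sponsor should set the number, record it before any outcome data are examined, and reconcile the definition with the intervention described under Osteopathic interventions.
2. State that the control-arm rule covers visceral mobilisation by a practitioner as well as self-mobilisation, and say how the two are counted.

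Label the per-protocol result explicitly as supportive, since exclusion on adherence after randomisation is selective under either definition.

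Both changes use the session records and booklet entries already planned; the only check needed is that the booklet separates osteopathic treatment from other non-medical care. Status and timeline puts the end of recruitment in January 2027 and the end of data collection in January 2028, so on the planned schedule the change can be made before analysis. The downside is a somewhat smaller per-protocol set and a wider interval.

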### Sample size

The required number of subjects is based on a comparison between the two randomized groups (experimental group *vs*. control) of the percentage variation in EHP-30 questionnaire scores between the pre-operative visit and at 1 year, with a two-sided first-species risk of error of 5%. For ethical reasons, we chose a 2:1 ratio for randomization.

In the literature, Goncalves et al. reported on the evolution of EHP30 scores (before/after) for a control and treatment group receiving an intervention (yoga sessions) [43]. Variations were small in the control group for the 5 main EHP-30 dimensions, and ranged from 20 to 35 points for the treatment group. Pokrzywinski et al [44]. showed the same before/after differences for a control and treatment group (Elagolix molecule), and defined thresholds of between 20 and 35 points for clinically significant differences.

To demonstrate a difference of 20 points associated with a standard deviation of 25, in percentage variation for EHP-30 questionnaire scores between the pre-operative visit and 1 year, with a statistical power greater than 80%, 38 patients are required in the experimental group and 19 in the control group. To allow for patients leaving the protocol and loss to follow-up, 10% more patients are required in each group. Thus, a total of 63 patients will be recruited (42 in the experimental group and 21 in the control group).

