The main analysis will be based on a comparison between the experimental and control groups using a Student’s t test or a Wilcoxon test according to distribution (Gaussian or not). Results will be expressed in terms of effect size and associated 95% confidence intervals.

The main analysis will be supplemented by a multivariate analysis of the linear regression type, to take into account covariates selected on the basis of univariate analysis results and their clinical relevance, including age, contraception and previous use of osteopathic mobilization. If necessary, the dependent variable under study may be modified. Particular attention will be paid to the study of multicollinearity (Farrar and Glauber test and VIF indicator) and to the conditions of the model application, notably the normality of residuals. Results will be expressed in terms of regression coefficients and 95% confidence intervals. Subgroup analyses will be proposed for the primary endpoint. The group x subgroup interaction, derived from the linear model described for the main multivariate analysis, will be analyzed and the result expressed in terms of associated regression coefficients and 95% confidence intervals.

Changes in quantitative evaluation criteria (secondary objective 1) based on longitudinal data (measurements repeated over time) will be studied using linear mixed models. These models take into account the correlation of measurements for the same patient. The patient will therefore be considered as a random effect in the model. Time will be considered as both a fixed and a random effect, with dependent variable transformation if necessary. Multivariate models will be considered. The comparison between the two randomization groups will be evaluated by adding the group and its interaction with time as fixed effects to the model. Models can be adjusted for age and contraception, and variable selection can be performed. Results will be expressed in terms of regression coefficients and 95% confidence intervals. Similarly, developments in qualitative evaluation criteria (secondary objective 4) will be based on generalized mixed models of the logistic type. Results will be expressed in terms of odds ratio and 95% confidence intervals.

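### The questionnaire mixed models estimate a difference in change from baseline; adjusting for the pre-operative score would be equally valid and, under most covariance patterns, more precise

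*Protocol article*

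**What the plan says.** The Outcomes section lists five questionnaires under secondary outcome 1a (EHP-30, GIQLI, FSFI, ICIQ-FLUTS, PCS), "evaluated at the pre-operative visit, and at 6 and 12 months". In Statistical methods, changes in the quantitative criteria of secondary objective 1 "based on longitudinal data (measurements repeated over time) will be studied using linear mixed models". The patient is a random effect, and "Time will be considered as both a fixed and a random effect". The arm comparison "will be evaluated by adding the group and its interaction with time as fixed effects to the model".

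Two statements concern covariates. For these models: "Models can be adjusted for age and contraception, and variable selection can be performed". More generally, comparisons are made without adjustment and then with adjustment for factors that turn out unbalanced, "such as contraception, level of disease severity and post-operative complications". Neither names the pre-operative score, and nothing sets the arms to a common pre-operative mean.

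No single sentence says that the pre-operative score is a response. That follows from reading the visit list together with a model for changes over repeated measurements.

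**The concern.** With the pre-operative score among the responses and a free group term, that term (with time categorical and the pre-operative visit as reference) is the difference between arms before surgery. Randomisation makes this difference zero in expectation, so estimating it spends information on a quantity already known by design. The group-by-time contrast then subtracts the whole observed baseline difference, although the follow-up scores carry only part of it.

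Precision is what is at stake. The trial plans for 19 evaluable controls, the results are to be reported as coefficients with 95% confidence intervals, and the study calls itself a pilot for a larger one. Interval width is therefore much of what these secondary analyses have to offer.

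**Working it through.** **Inputs.** From Sample size: 38 experimental and 19 control evaluable patients, a 20-point difference, SD 25, two-sided 5%, power above 80%. From Outcomes: three visits (pre-operative, 6 and 12 months). Assumed, because the article gives no value: rho, the correlation between visits, and k, the ratio of post- to pre-operative SD.

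**The plan's own figure.** Control n = (1 + 1/2) × (1.960 + 0.842)² × 25² / 20² = 18.4, rounded up to 19, hence 38 experimental. Power at 38 + 19 is 81.3% by the normal approximation and 79.9% by the noncentral t. The plan's numbers are reproduced.

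**What the planned model estimates.** With complete data and categorical time, group × 12 months equals the raw difference in mean change. In one simulated data set of 57 patients the fitted coefficient was −4.686 and the raw difference in change was −4.686.

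**Effect of a chance baseline difference d (equal SDs).** The 12-month difference is expected to move by rho × d. The change contrast subtracts d, so it moves by −(1 − rho)d, which is 70%, 50% or 30% of d at rho 0.3, 0.5 or 0.7.

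**Variance, equal SDs and compound symmetry.** Per patient, with visit SD σ:
- change from baseline: 2σ²(1 − rho)
- baseline-adjusted or common baseline: σ²(1 − rho²)
- ratio: (1 + rho)/2, a reduction of (1 − rho)/2

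Taking 25 as the SD of change, the planned SE is 25 × √(1/38 + 1/19) = 7.02. The adjusted SE is 7.02 × √((1 + rho)/2).

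| rho (assumed) | Planned SE | Adjusted SE | Variance reduction | Illustrative EHP-30 power, 20 points |
|---|---|---|---|---|
| 0.3 | 7.02 | 5.66 | 35% | 0.81 → 0.94 |
| 0.5 | 7.02 | 6.08 | 25% | 0.81 → 0.91 |
| 0.7 | 7.02 | 6.48 | 15% | 0.81 → 0.87 |

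At rho 0.8 the reduction is 10%. A 20,000-run simulation at rho 0.5 gave a variance ratio of 0.76 against the theoretical 0.75, with mean estimates of 0.01 (change) and −0.02 (adjusted) when there was no effect. If time is linear instead of categorical, the planned SE is still 7.02 and the ratios are 0.60, 0.73 and 0.84.

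**Unequal SDs.** With pre-operative SD 1 and post-operative SD k, the variances are 1 + k² − 2k·rho (change) and k²(1 − rho²) (adjusted). They differ by (1 − k·rho)², which is never negative. At rho 0.7:
- k = 0.8: 0.520 and 0.326, reduction 37%
- k = 1.2: 0.760 and 0.734, reduction 3%
- k = 1.4: 1.000 and 0.9996, reduction about 0%

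**Random time slope.** The plan makes time a random effect, which compound symmetry does not include. Take intercept variance rho, residual variance 1 − rho, and an uncorrelated slope whose variance over 12 months equals the residual variance. The 12-month variance is then 2 − rho and its covariance with baseline is rho. The variances are 3(1 − rho) for change and (2 + rho)(1 − rho) adjusted, a ratio of (2 + rho)/3. The reductions are 23%, 17% and 10% at rho 0.3, 0.5 and 0.7, where rho is the within-patient correlation without the slope.

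**The case against.** The strongest reply is that nothing here is an error. Group plus group-by-time is a standard and unbiased comparison in a randomised trial. The models are secondary, some secondary analyses are described as mainly exploratory, and the wording on covariates is permissive. This stands, and it limits the point to a matter of efficiency. It does not remove the point, because the article states the terms of the comparison instead of leaving them to a later plan.

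A second reply is that the general adjustment rule is open-ended, so a pre-operative score could enter under it. That is possible, but the trigger is observed imbalance. Baseline adjustment improves precision whether or not imbalance is seen, and adding it only when imbalance appears would be data-driven.

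Third, the covariance is not specified. This also stands: the 35%, 25% and 15% figures belong to one structure, and surgery lies between the visits, so equal SDs cannot be taken for granted.

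Four stronger readings are tempting, and the documents do not support them:
- *The planned contrast is biased.* It is not; the two approaches have the same expectation under randomisation.
- *A chance baseline difference passes in full into each contrast.* With equal SDs, only (1 − rho) of it is expected to.
- *The power gain applies to all five questionnaires.* The 20 points and SD 25 are given for EHP-30 variation only. No SD or target difference is given for GIQLI, FSFI, ICIQ-FLUTS or PCS.
- *A common baseline mean can simply be imposed.* The article's text does not say whether questionnaires are completed before allocation is known. Blinding is described only for the one-year osteopath, and the experimental arm has a pre-operative session. If answers can be influenced by allocation, forcing equal baselines could introduce bias.

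**Conclusion.** The point holds as an efficiency improvement to the secondary-objective-1 questionnaire models. The planned contrast is valid, but it is a difference in change scores and uses the pre-operative score less well than it could.

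The variance reduction available at 12 months is 15% to 35% for rho from 0.7 down to 0.3 under equal variances and compound symmetry. Over the wider range of covariance patterns examined it runs from about nil to over a third. In large samples the adjusted estimator is not less precise; at this sample size, estimating the baseline slope costs a little.

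This rests on the pre-operative score being a response, on assumed values of rho and k, and on complete data. The SEs and power figures also read SD 25 as the SD of change in points, which makes them illustrative for EHP-30 only. The primary Student or Wilcoxon test is outside the point and is unchanged.

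**What to change.** In Statistical methods, replace the sentence on the arm comparison for the secondary-objective-1 questionnaires with one of these:
- The 6- and 12-month scores are the responses, with visit, group, group × visit and the pre-operative score as a pre-specified covariate.
- Equivalently with complete data under the equal-variance model above, all three visits are responses with one common pre-operative mean, and group enters only through its interaction with the post-operative visits.

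Report the 6- and 12-month group differences with 95% confidence intervals. State that the baseline questionnaire is completed before allocation is known. If that cannot be confirmed, do not impose the common mean, and treat the baseline as potentially affected by allocation.

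In the covariate form each patient has only two responses. A correlated random intercept and slope plus a residual would have four variance parameters for three distinct covariance elements, so a random intercept or an unstructured 2 × 2 covariance should replace the random time effect.

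The cost is a sentence or two of text. No further patients, visits or data are needed, and data collection is scheduled to end in January 2028, so the change can be made well before analysis.
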